#### Timeline and assessments

2.4.2

According to the flowchart of the study (Figure 1), participants will undergo six different steps.

*Baseline T0* (post-diagnosis, pre-hospitalization, pre-surgery): Participants will complete clinical interview and self-report psychological assessment battery.*Surgery:* participants will undergo breast surgery.*Follow-up T1* (within 1 week post-surgery): Participants will complete clinical interview and repeat self-report instruments to evaluate temporal changes.*Group assignment:* Following T1 assessment, participants will be randomly assigned to one of three groups, then follow their respective 8-week psychological intervention.*Follow-up T2* (psychological intervention completion, within 3 months post-surgery): All participants will complete the psychological assessment battery again to evaluate temporal changes.*Follow-up T3* (within 3 months post-psychological intervention): All participants will complete the psychological assessment battery again.

Participants who withdraw (dropout) from the study will not have their data considered in analyses. However, these individuals will continue receiving treatment benefits from their assigned condition. To ensure complete and optimal data analysis, questionnaires presenting missing data will be excluded from the study (Pozzar et al., 2020) – though participants will continue benefiting from assigned treatment.

### Outcome measures

2.5

In accordance with study objectives, this research protocol assesses a comprehensive range of psychological outcomes relevant to breast cancer patients, including affective symptoms, trauma-related distress, body image, self-esteem, emotion regulation difficulties, perceived social support, and global psychological functioning.

An anamnestic form will collect sociodemographic variables (age, marital status, education, family composition, employment status, current intimate relationship information), immigration status, alcohol consumption, substance abuse, and notable life events (separation, bereavement, etc.). Additionally, beyond standard clinical interview, temporal changes will be monitored using validated Italian-language self-report instruments.

All assessments will be administered at baseline (T0), after surgical intervention (T1), after completion of the psychological intervention (T2), and at 3-month follow-up from the complention of the psychological intervention (T3) - to evaluate long-term changes.

#### Primary outcomes

2.5.1

Based on the theoretical framework previously outlined, primary outcomes were selected to assess the core psychological constructs targeted by the intervention: psychological distress and post-traumatic symptomatology following breast cancer diagnosis and surgery.

##### Psychological distress inventory – revised (PDI-R)

2.5.1.1

The PDI-R (Rossi et al., 2022) is a self-report questionnaire specifically created for distress measurement in oncological settings. Comprising 8 items, it is suitable for medical setting test batteries. Beyond providing total distress score, clinical cut-offs and normative scores divided by sex and age have been developed. The instrument’s psychometric properties proved excellent.

##### Post-traumatic symptom questionnaire (PTSQ)

2.5.1.2

The PTSQ (Rossi et al., 2024b) is a 12-item questionnaire developed to evaluate post-traumatic stress symptoms (PTSS) and traumatic event impact across three components: (i) intrusion, (ii) avoidance, and (iii) hyperarousal. Given its administration agility, the PTSQ particularly suits PTSS measurement across diverse contexts (Rossi et al., 2024c) compared with lengthier instruments (Rossi et al., 2024a). Beyond providing scores for the three mentioned components, the PTSQ yields total score with developed clinical cut-offs (Rossi et al., 2024a). Psychometric properties proved excellent.

#### Secondary outcomes

2.5.2

Secondary outcomes were selected to capture additional dimensions of psychological functioning relevant to breast cancer patients, including anxiety and depressive symptomatology, hopelessness, body image, and global psychological wellbeing.

##### Hospital anxiety and depression scale (HADS)

2.5.2.1

The HADS (Zigmond and Snaith, 1983; Norton et al., 2013) is among the world’s most utilized self-administered tests for evaluating anxious and depressive symptomatology in medical/organic settings. The HADS comprises 14 items, yielding two scores: anxiety scale and depression scale. In the present study, the two subscales will be used separately to assess anxiety and depressive symptomatology as distinct outcomes. The Italian version (Annunziata et al., 2011) demonstrated excellent psychometric properties.

##### Beck hopelessness scale (BHS)

2.5.2.2

The BHS (Beck et al., 1985) is a self-report test specifically created for evaluating hopelessness feelings – a key psychological element in treating complex medical conditions like depression. It comprises 20 dichotomous items (true/false). The Italian version (Iliceto and Fino, 2015) showed excellent psychometric properties.

##### Body image scale (BIS)

2.5.2.3

The BIS (Hopwood et al., 2001; Melissant et al., 2018) is a self-administered questionnaire specifically developed for body image evaluation in patients with medical/organic and oncological pathologies. Comprising 10 items, it yields a single total score. The Italian version (Cheli et al., 2016) demonstrated good psychometric properties.

##### Difficulties in emotion regulation scale – 8 (DERS-8)

2.5.2.4

The DERS-8 (Penner et al., 2023) is an 8-item measure assessing emotion regulation difficulties (Gratz and Roemer, 2004) as a single dimension. Items cover difficulties in acceptance, goal-directed behavior under distress, impulse control, and access to effective regulation strategies. The Italian version (Rossi et al., 2025) demonstrated excellent psychometric properties.

##### Rosenberg self-esteem scale (RSES)

2.5.2.5

The RSES (Rosenberg, 1965) is a widely used 10-item measure assessing global self-esteem in general and clinical populations, defined as an individual’s overall evaluation of their own worth. The Italian version (Prezza et al., 1997) demonstrated good psychometric properties.

##### Psycho-social support scale (PSSS)

2.5.2.6

The PSSS (Panzeri et al., 2022) is a brief 4-item self-report measure assessing perceived psycho-social support, capturing the extent to which individuals feel supported by their social environment. Higher scores indicate greater perceived support. The scale demonstrated good psychometric properties.

##### Clinical outcomes in routine evaluation – outcome measure (CORE-OM)

2.5.2.7

The CORE-OM (Evans et al., 2000) is among the world’s most utilized instruments for evaluating general symptomatology and suicidal risk. It examines four distinct psychological functioning domains: (1) subjective wellbeing; (2) problems and symptoms; (3) social and psychological functioning; and (4) self/other-harm risk. The Italian version (Palmieri et al., 2009) demonstrated good psychometric properties.

### Statistical analysis

2.6

Statistical data analyses will be performed using R software (R Core Team, 2017). Throughout data collection duration, *in itinere* statistical analyses will verify data quality and potential bias absence. Regarding missing data management, participants who discontinue the study (dropouts) will be excluded from analyses due to concerns about response validity. Similarly, assessment batteries with more than 10% missing items will be considered invalid and excluded. For remaining missing data within valid batteries, appropriate handling methods (e.g., multiple imputation, full information maximum likelihood) could be employed depending on missing data patterns and mechanisms.

Preliminary analyses will verify group homogeneity regarding relevant variables (age, comorbidity, social support, etc.) and possible intervening variable influence (covariates). If deemed appropriate and/or if significant heterogeneity is detected between groups, such variables will be included as covariates in the analysis models. Preliminary analyses will also verify psychometric instruments’ internal consistency (McDonald’s omega) (McDonald, 1999).

Both group-level aggregate analyses and individual change-focused evaluations will be employed. At group level, longitudinal changes will be examined using appropriate linear models for repeated measures data (e.g., linear mixed models or repeated measures ANOVA, or Bayesian approaches), depending on data characteristics such as distribution, missing data patterns, and sphericity assumptions (Howell, 2013; Darlington and Hayes, 2017; van den Bergh et al., 2023). Also, if appropriate, multilevel analysis – random slopes and/or random intercepts – may be implemented in the models (Hox et al., 2017; Heck and Thomas, 2020; Finch and Bolin, 2024). Model selection will be guided by standard diagnostic procedures. All models will test the interaction between time and intervention group – and where appropriate – controlling for individual variability and potential covariates identified in preliminary analyses.

Additionally, between-group comparisons at each timepoint may be performed using appropriate statistical tests depending on data distribution (e.g., one-way ANOVA or Kruskal-Wallis). If appropriate, post-hoc pairwise comparisons (R-TEP vs. TAU, R-TEP vs. psychoeducation, psychoeducation vs. TAU) will be conducted to identify specific group differences. Within-group comparisons across timepoints (e.g., T0 vs. T1, T1 vs. T2) may also be examined to evaluate change trajectories within each condition. Effect sizes (e.g., Cohen’s d for pairwise comparisons, partial η^2^ for omnibus tests) will be reported to facilitate clinical interpretation (Cohen, 1988). If necessary, to control for Type I error inflation due to multiple testing, the False Discovery Rate (FDR) correction procedure will be applied to the primary outcomes (Benjamini and Hochberg, 1995; Storey, 2002). Secondary outcomes will be analyzed as exploratory. Moreover, if Bayesian approaches are employed, Bayes Factors will be reported to quantify evidence strength for both alternative and null hypotheses (Greenland and Poole, 1994; Kass and Raftery, 1995; Lavine and Schervish, 1999; Held and Ott, 2018).

At individual level, parameters identifying significant changes both statistically (e.g., Reliable Change Index) and/or clinically (e.g., Minimal Clinically Important Difference) could be calculated (Maassen, 2000, 2001; Turner et al., 2010). Additionally, when available, individual scores will be compared with normative scores (expressed in Z or T points) to evaluate symptom severity relative to reference population (Howell, 2013; Tabachnick and Fidell, 2019).

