#### Sample size calculation

2.2.4

An *a priori* power analysis was conducted to calculate the minimum sample size required for this study, following established statistical procedures (Perugini et al., 2018; Taccini et al., 2022). The G*Power software (V.3.1.9.2) (Faul et al., 2007, 2009) was utilized to determine the required sample size for repeated measures analysis of variance (ANOVA) with within-between interaction. The research protocol involves four assessment timepoints, with treatment condition as between-group variable (TAU vs. TAU + psychoeducation vs. TAU+R-TEP) and time as within-subject variable (T0, T1, T2, and T3; see dedicated section).

Given the absence of prior studies implementing this specific intervention protocol, conservative a priori parameters were adopted. These were informed by examining previous studies utilizing similar interventions (though not identical), comparable target samples, and similar constructs. The effect size *f* was set to 0.15 (small-to-medium effect size) and the correlation among repeated measures was set to 0.35. Type I error rate probability (*α*) was set to 0.05 (two-sided), and power (1-*β*) was set at 0.80 (Cohen, 1988; Eid et al., 2017; Perugini et al., 2018).

G*Power analysis indicated 80% probability of correctly rejecting the null hypothesis of no significant group-by-time interaction effect with an overall sample of 102 participants (approximately 34 subjects per group). Based on average patient flow to the unit, to account for an anticipated attrition rate of approximately 20%, the study aims to recruit at least 122 patients, ensuring adequate statistical power for the planned analyses.

The three groups will each comprise a minimum of 34 patients: (A) Control group (G1): Patients receiving standard routine psychological support (TAU); (B) Active control group (G2): Patients receiving weekly psychoeducation session plus TAU; (C) Experimental group (G3): Patients receiving EMDR R-TEP intervention plus TAU.

This sample size is highly feasible considering service patient flow while simultaneously permitting statistical analyses generating reliable estimates.

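### Dropouts are removed with all their data, including valid scores given before leaving, so the comparison is completers-only and open to bias when dropout differs by arm

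*Protocol article*

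**What the plan says.** The exclusion rule appears twice in the protocol article.

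- Section 2.6, Statistical analysis: "participants who discontinue the study (dropouts) will be excluded from analyses due to concerns about response validity".
- Section 2.4.2, Timeline and assessments: "Participants who withdraw (dropout) from the study will not have their data considered in analyses".

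Both act on the whole participant. Section 2.6 has a separate validity rule, under which an assessment battery with more than 10% of items missing is discarded. It offers multiple imputation and full information maximum likelihood only for gaps inside batteries that pass that rule. For the group-level analysis it names linear mixed models, repeated measures ANOVA or Bayesian approaches, and it fixes the time-by-group interaction as the test in every model.

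The sample size section (2.2.4) expects the loss: "to account for an anticipated attrition rate of approximately 20%, the study aims to recruit at least 122 patients". The article describes no intention-to-treat or sensitivity analysis that brings these patients back, and the limitations section does not mention their exclusion.

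**The concern.** The stated reason is response validity, but leaving the study later does not make earlier answers invalid. The 10% rule already screens battery quality, so the dropout rule removes batteries that have passed that screen. Section 2.4.2 randomises after T1, so on that timetable a patient who drops out after randomisation will normally already have T0 and T1 scores, and may have T2.

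Randomisation protects the comparison of everyone randomised. It does not protect a comparison of those who stayed. The outcomes are distress and post-traumatic symptoms, session content differs by arm, and sections 2.3.2 and 2.3.3 expect transient distress or emotional activation in the two structured arms. Dropout that depends on symptom level, and does so differently by arm, is therefore plausible. If it occurs, deleting the leavers' observed scores shifts the group means by different amounts, and the shift can pass for a treatment effect or hide one.

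**Working it through.** **1. The plan's own sample size.** Inputs from section 2.2.4: the design is "required sample size for repeated measures analysis of variance (ANOVA) with within-between interaction", with k = 3 groups and m = 4 timepoints; the effect size f "was set to 0.15 (small-to-medium effect size) and the correlation among repeated measures was set to 0.35"; alpha is 0.05 and power 0.80. Sphericity is assumed.

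- Noncentrality: λ = f² × N × m / (1 − ρ). With N = 102: 0.0225 × 102 × 4 / 0.65 = 14.12.
- df1 = (k − 1)(m − 1) = 6; df2 = (N − k)(m − 1) = 297.
- Power at N = 102 is 0.807. The smallest N reaching 0.80 is 101 (0.802), which becomes 102 with three equal groups. The stated figure reproduces.

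**2. How many are lost, and the effect on power.**

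- 0.20 × 122 = 24.4 patients removed; 122 − 24.4 = 97.6 remain.
- The remainder is below 102 because 122 is 102 × 1.2 (122.4), whereas 102 / 0.80 = 127.5, or 128.
- Power is 0.783 with 97 completers and 0.788 with 98. If all 122 contributed complete data it would be 0.883. A mixed model using partial records lies between these bounds.

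Against the planned 0.80 the shortfall is under two percentage points.

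**3. Which data the rule deletes.** Taking the rules of section 2.6 in order, dropouts go first, then batteries with more than 10% of items missing, and imputation or full information maximum likelihood applies to what is left. The model therefore never receives a dropout's scores, whichever model is chosen. A mixed model fitted by maximum likelihood accepts incomplete patient records. Classical repeated measures ANOVA needs complete ones, so the point about usable partial data applies to the former only.

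**4. Illustration of the bias.** The mechanism is assumed; the documents give none. There is no true effect, all four timepoints have SD 1 and pairwise correlation 0.35 (the plan's value), and dropout occurs between T2 and T3 with logit P(drop) = −1.5 + s × T2. Attrition is 22% for s = ±1 and 18% for s = 0. Completer means for s = +1 are about −0.07 at T0, T1 and T3, and −0.19 at T2. For s = −1 they mirror this, and for s = 0 they are 0.

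| Bias in the between-arm difference (SD, absolute) | s = 1 in one arm, 0 in the other | s = +1 and −1 (extreme) | same s in both arms |
|---|---|---|---|
| T2 alone | 0.19 | 0.38 | about 0 |
| T3 alone | 0.07 | 0.13 | about 0 |
| Change T1 to T2 | 0.12 | 0.25 | about 0 |
| Change T1 to T3 | about 0 | about 0 | about 0 |

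The change rows bear on the planned interaction test. In the one-arm case, 0.19 − 0.07 = 0.12 at T2. At T3 the T1 and T3 means shift equally, so the difference cancels. In the extreme case, 0.38 − 0.13 = 0.25.

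Dropout here depends only on an observed score, so it is missing at random given T2. The T2 bias arises entirely from deleting T2 scores that were collected, and a likelihood-based analysis of all observed scores has bias of about 0.

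**5. A second mechanism.** With 20% dropout per arm driven by the T1 score (slope 0.5 to 1 in one arm, 0 to −1 in the other), the completers-only difference at T3 alone is off by 0.03 to 0.12 SD. Using T0 and T1 from all patients brings it to about 0. With the same slope in both arms it is about 0 from the start.

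**The case against.** Several points on the other side are sound.

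- **Size on the planned test.** A reader might take the single-timepoint figures (0.38 and 0.19 SD at T2, 0.13 and 0.07 SD at T3) as the bias in the primary analysis. The fixed test is the group-by-time interaction; comparisons at each timepoint are only optional in section 2.6. For change from T1 the figures are smaller at T2 and about 0 at T3, which is where section 3.1 expects the clearest advantage for R-TEP.
- **Plausibility of the scenario.** Nothing in the article supports opposite-direction dropout at odds of about 2.7 per SD. That case is a bound. If the mechanism is common to the arms, no between-arm bias results.
- **Power.** A reader might infer a serious loss. The plan already inflates for attrition, and the shortfall is minor.
- **The share lost.** A reader might infer that 20% of randomised patients vanish. The 20% is a planning figure for recruited patients. Section 2.4.2 randomises after T1, so some loss may come before randomisation. Section 2.2.5 instead counts seven working days from baseline.
- **Further follow-up.** Section 2.4.2 keeps dropouts in treatment, and a reader might infer that many would still complete T2 and T3. The article defines dropouts as people who leave the study and says nothing about their willingness to answer questionnaires. Nor does it say that one missed assessment counts as dropout.
- **Data deletion.** Section 2.4.1 lets a withdrawing participant have her data deleted. Those data cannot be used, but deletion is optional and does not justify removing every dropout.

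These points limit the size of the problem. None of them restores the excluded scores or supports the reason given for excluding them.

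**Conclusion.** The concern holds. As written, the rule discards valid scores collected before dropout and turns a randomised comparison into one of completers. About 24 of 122 recruited patients would be affected at the planned attrition, with the randomised share possibly somewhat lower. The harm is potential bias, conditional on dropout relating to scores differently by arm: about 0.12 SD in the T1-to-T2 change contrast for a one-arm mechanism, about 0.25 SD as an extreme, and about 0 for change to T3 or under a common mechanism. These sizes rest on the assumed slopes, equal correlations of 0.35 and T2-driven dropout. The zero for change to T3 also depends on those assumptions and is no general assurance. The documents do not support a claim of large power loss, or of a bias of 0.38 SD in the planned interaction test.

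**What to change.** Replace the dropout sentences in sections 2.4.2 and 2.6 with one rule: all randomised patients are analysed in their assigned group with every valid score they provided, except where a participant requests data deletion. The existing limit of 10% missing items can still define a valid battery.

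Name the linear mixed model, fitted by (restricted) maximum likelihood under missing-at-random, as the primary analysis, so that partial records are used. Report dropout by arm with reasons. Keep the completers-only analysis as a sensitivity analysis; a missing-not-at-random sensitivity analysis is a useful option.

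The cost is slightly more analysis and a wording change which, under section 2.7, is notified to the ethics committee and updated in the registry. No extra patients or visits are needed. The change should be made before outcome data are seen.

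### The two missing-item rules conflict, and the battery-level 10% rule can discard complete primary scores because a long secondary scale is blank

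*Protocol article*

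**What the plan says.** The protocol article deals with missing items in two places.

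- Section 2.4.2 (Timeline and assessments): "questionnaires presenting missing data will be excluded from the study". No tolerance is given and imputation is not mentioned. The participant continues treatment.
- Section 2.6 (Statistical analysis): "assessment batteries with more than 10% missing items will be considered invalid and excluded". It then adds: "For remaining missing data within valid batteries, appropriate handling methods (e.g., multiple imputation, full information maximum likelihood) could be employed", depending on the pattern and mechanism of missingness.

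The co-primary scales are short. Of the PDI-R, section 2.5.1.1 says "Comprising 8 items, it is suitable for medical setting test batteries"; the PTSQ, in section 2.5.1.2, "is a 12-item questionnaire developed to evaluate post-traumatic stress symptoms". Some secondary scales are longer: for example, "The HADS comprises 14 items, yielding two scores", and the BHS has 20 items (section 2.5.2.2). No item count is given for the CORE-OM (section 2.5.2.7). Section 2.6 treats secondary outcomes as exploratory and sets no separate completeness criterion for the PDI-R or PTSQ.

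**The concern.** The two sections differ in three respects: the unit (questionnaire or battery), the threshold (any gap or more than 10%) and the handling (exclude or possibly impute). A PDI-R with one blank item in an otherwise complete battery is excluded under one section and kept under the other. Two analysts could follow the protocol faithfully and obtain different data sets for the primary outcomes, and the choice could be made after the data are seen.

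The section 2.6 rule has a further weakness. Because it pools all items at a visit, the fate of the primary scores depends on how much of the battery the skipped items make up, not on whether the primary scales were answered. Long exploratory scales therefore carry the most weight. Gaps on scales about hopelessness or mood may plausibly be related to distress, which is itself a primary outcome, so the loss could bring bias as well as imprecision. The documents give no data on how often this would happen.

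The sample size has no reserve for such losses. Section 2.2.4 inflates 102 to 122 for attrition alone, and 122 × 0.80 = 97.6 is already below 102.

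**Working it through.** **Plan's own figure.** The plan gives no number for losses from missing items. The nearest figure, 102 participants in section 2.2.4, reproduces. For the group-by-time interaction with 3 groups, 4 visits, f = 0.15 and ρ = 0.35, λ = f²·N·m/(1−ρ) = 0.0225 × 102 × 4/0.65 = 14.1. With 6 and 297 degrees of freedom, power is 0.807. Nothing below depends on it.

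**Inputs (section 2.5).** PDI-R 8, PTSQ 12, HADS 14, BHS 20, BIS 10, DERS-8 8, RSES 10, PSSS 4. The sum is 86. The CORE-OM length is unstated; call it c. I take the battery to be the listed self-report scales at one visit, 86 + c items.

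**Step 1: which blank scale invalidates the battery?** A wholly blank scale of s items is s/(86 + c) of the battery. It triggers exclusion when s/(86 + c) > 0.10, that is, when c < 10s − 86.

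- BHS: c < 200 − 86 = 114.
- HADS: c < 140 − 86 = 54.
- BIS or RSES: c < 100 − 86 = 14.
- DERS-8: at most 8/86 = 9.3%, so never. PSSS: at most 4/86 = 4.7%, so never.
- CORE-OM itself: c/(86 + c) > 0.10 requires 9c > 86, so c of 10 or more.
- PTSQ (primary): c < 120 − 86 = 34.
- PDI-R (primary): at most 9.3%, so never.

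Share of the battery that is missing, over an assumed range of c (c = 0 is only a bound, since the CORE-OM is administered):

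| Only this scale blank | c = 0 (86 items) | c = 20 (106) | c = 40 (126) |
|---|---|---|---|
| BHS | 23.3% | 18.9% | 15.9% |
| HADS | 16.3% | 13.2% | 11.1% |
| BIS or RSES | 11.6% | 9.4% | 7.9% |
| PTSQ | 14.0% | 11.3% | 9.5% |
| PDI-R or DERS-8 | 9.3% | 7.5% | 6.3% |
| PSSS | 4.7% | 3.8% | 3.2% |

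A blank BHS or HADS exceeds 10% throughout, so complete PDI-R and PTSQ scores at that visit go with it. If the anamnestic form were also counted as part of the battery, the denominator would grow: the BHS result holds up to 199 items in total and the HADS result up to 139.

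**Step 2: loss under the section 2.4.2 rule.** Let each item be skipped independently with probability p. This is an assumption; the documents give no skip rate. The probability that a k-item scale has at least one gap is 1 − (1 − p)^k at one visit and 1 − (1 − p)^(4k) over four visits.

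| | p = 0.5% | p = 1% |
|---|---|---|
| PDI-R, one visit (8 items) | 1 − 0.995^8 = 3.9% | 1 − 0.99^8 = 7.7% |
| PTSQ, one visit (12 items) | 1 − 0.995^12 = 5.8% | 1 − 0.99^12 = 11.4% |
| PDI-R, four visits (32 items) | 1 − 0.995^32 = 14.8% | 1 − 0.99^32 = 27.5% |
| PTSQ, four visits (48 items) | 1 − 0.995^48 = 21.4% | 1 − 0.99^48 = 38.3% |

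The one-visit rows apply if the analysis uses all available visits, as a linear mixed model does. The four-visit rows apply if a patient needs complete data at every visit, as repeated measures ANOVA ordinarily requires. Section 2.6 lists both methods.

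**The case against.** The best defence is that the section 2.6 threshold is a validity screen for carelessly completed batteries, that detailed scoring rules belong in a full protocol or SAP that is not shown, and that nothing indicates how often a patient leaves an entire BHS or HADS blank. The last point stands: the frequency, and hence the bias, cannot be quantified from the documents. The first two do not remove the problem. The article states the rule twice, incompatibly, and a screen that rejects fully answered primary scales because another scale is blank does not measure the validity of the primary scales.

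Some stronger readings are tempting but unsupported.

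- *Accepting a battery with a blank PDI-R is an error.* It shows that the threshold does not track completeness of the primary outcomes. But section 2.6 calls only the battery valid and allows the gap to be handled by imputation or FIML. Treating that PDI-R score as missing and keeping the other scales is sound.
- *Any blank secondary scale discards the primary data.* Step 1 shows this for the BHS and HADS, and for the CORE-OM if it has at least 10 items, but not for the short scales.
- *Section 2.4.2 leaves nothing to impute.* It removes item-level gaps, but an excluded questionnaire still leaves a missing scale score that multiple imputation or FIML could handle.
- *The section 2.6 rule removes patients.* It removes one visit's battery. The patient is lost only if the chosen model needs every visit.
- *Only 67% or 45% of patients would be complete.* These are 0.995^80 and 0.99^80, which require both primary scales to be complete at all four visits. The PDI-R and PTSQ are separate outcomes, so the per-outcome figures above are the relevant ones.

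**Conclusion.** The point holds, as a matter that should be fixed. The contradiction between sections 2.4.2 and 2.6 rests on the text alone. The battery-unit defect rests on the stated item counts and on reading the battery as the scales given at one visit. It is robust to the missing CORE-OM length, holding for the BHS at any c below 114 and for the HADS at any c below 54.

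The size of the section 2.4.2 loss is conditional. At assumed independent skip rates of 0.5% to 1%, it is about 4–8% of PDI-R and 6–11% of PTSQ scores per visit. If all four visits must be complete, it is 14.8–27.5% and 21.4–38.3% of patients. Real skipping probably clusters within patients, so these figures illustrate and do not predict. The documents do not show that the primary conclusion would change.

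**What to change.** Delete the section 2.4.2 sentence on questionnaires with missing data, and restate the section 2.6 rule per questionnaire:

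- Each scale is scored on its own, and a blank secondary scale never removes the PDI-R or PTSQ.
- Within a scale, prorate or impute items when at least a stated share is answered (half, for example).
- Below that share, the scale score at that visit is missing and is handled in the mixed model or by multiple imputation. No patient is removed for missing items.

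The 10% figure should not simply be carried over to single scales. One blank PDI-R item is 1/8 = 12.5% and would fail, while one blank PTSQ item is 1/12 = 8.3% and would pass.

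The cost is two sentences and no extra data. The downside is a modest assumption in prorating or imputing items.
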